### Adverse events

Adverse events are defined as any undesirable experience (harmful, objectionable, or unpleasant) occurring to a patient during the study, whether or not considered related to the testing procedures or the experimental intervention. In the study information letter patients are instructed to contact the investigators in case of an adverse event. All adverse events reported spontaneously by the patient or observed by the research team will be recorded. A serious adverse event is any untoward medical occurrence or effect that results in death; is life threatening (at the time of the event); requires hospitalization or prolongation of existing inpatients' hospitalization; results in persistent or significant disability or incapacity; any other important medical event. The investigator will report all SAEs to the sponsor without undue delay after obtaining knowledge of the events.

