### Randomization, blinding and treatment allocation

This study is quasi-randomized and non-concealed. Patients will be screened in the first week of the multidisciplinary rehabilitation programme (2 weeks prior to baseline data collection). Enrolment and allocation will be 1 week prior to baseline data collection after consent of the patient. Patients will be enrolled and allocated to each intervention by one of the investigators ([name]) based on the starting date of the multidisciplinary rehabilitation programme. The research team has no influence on the starting date of each patient. If two patients start on the same date, allocation order will be alphabetically (based on the patients last name). The first five patients were allocated to the static motor control group, followed by five patients in the sensor-based movement control group and so forth until 30 patients have completed each intervention. This random allocation sequence was chosen by the investigators to keep group therapy planning feasible. Patients and therapists will not be blinded as this is practically impossible, however they will not be informed about the hypotheses of the study. The primary study outcome (spinal movement tracking error) will be calculated using a computer algorithm (custom made in D-flow, Motek, Amsterdam, The Netherlands) that will work independent of treatment allocation. Investigators involved in the statistical analysis will not be blinded to group. The clinical movement control battery tests will be recorded on video and scored by two examiners that are blinded to time (before/after intervention) and allocation.

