### Interventions

The Sensor-Based Movement Control and Static Motor Control intervention will be offered over a course of 8 weeks (weeks 2–9 of the study), each week consisting of two supervised therapy sessions of 20–30 min and four non-supervised home exercises of 5–10 min resulting in nearly one training session every day of the week for 8 weeks.

The supervised sessions are provided by five experienced (4–10 years) physio- and occupational therapists from the MRC that are trained to provide both the intended interventions. The therapists can also provide the regular therapies in the multidisciplinary rehabilitation programme of a patient. Three training moments are given to all therapists at the same time by the investigators to understand the content of the interventions and how to offer this to the patients during 8 weeks. The quality will be assured by several evaluation meetings with the investigators and investigators will check the content of the sessions by occasionally being present at the supervised sessions throughout the study. The first four sessions will be individual, i.e., one patient supervised by one therapist. In these sessions, the capacity of the patient will be determined by the therapists and the patient will get acquainted with the basics of the training. The final 12 sessions will be in groups, with a maximum of three patients in the same intervention per session, supervised by one therapist. The patients will not have the same therapist throughout the programme to keep the rehabilitation planning feasible. The therapists will monitor the progress and challenge the patient if needed during all sessions. There is a standard protocol for exercises throughout the sessions, for both the sensor-based movement control and static motor control group. This protocol was composed by two experienced physiotherapists/human movement scientists and are based on literature (6). Therapists are allowed to modify the standard exercises to match the difficulty level to the capacity of the patient. The standard exercises can also be deviated from to the need of the individual patient as long as it is within the scope of the assigned intervention. There is no standardized approach for modifications in progression, however all modifications will be registered. An example of the protocol for week four is presented in Figure 2. Attendance of the supervised sessions will be registered.

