### Safety considerations

The tests at the beginning and end of the intervention could result in a transient increase in low back pain. Training with sensors could result in spinal tissue overload as a result of lack of focus on bodily sensations. However, the Military Rehabilitation Center has more than 10 years of experience with providing a similar type of therapy in low back pain patients. Moreover, the complexity, duration and intensity of the exercises will be increased gradually, which would minimize the chance of overloading the spinal structures. Damage to research subjects through injury or death caused by the study is covered by the Ministry of Defense. This applies to the damage that becomes apparent during the study or within 4 years after the end of the study.

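### Adverse events are collected only passively although the protocol names an overload risk of sensor training; one identical question in both groups would close the gap cheaply

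*Protocol article*

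**What the plan says.** The Adverse events section of the protocol article defines events broadly: "Adverse events are defined as any undesirable experience (harmful, objectionable, or unpleasant) occurring to a patient during the study", whether or not related to the tests or the intervention. Collection is by two routes: "All adverse events reported spontaneously by the patient or observed by the research team will be recorded". The prompt to patients is a single written one: "In the study information letter patients are instructed to contact the investigators in case of an adverse event".

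The Safety considerations section names a possible hazard of one intervention and its mechanism: "Training with sensors could result in spinal tissue overload as a result of lack of focus on bodily sensations". It then offers two mitigations: the centre's long experience with similar therapy, and a gradual increase in exercise load.

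The Interventions section describes a week of training as "two supervised therapy sessions of 20–30 min and four non-supervised home exercises of 5–10 min", over 8 weeks. On who is present and what they do, it says that "investigators will check the content of the sessions by occasionally being present at the supervised sessions throughout the study" and that "The therapists will monitor the progress and challenge the patient if needed during all sessions". Under Randomization, blinding and treatment allocation: "Patients and therapists will not be blinded as this is practically impossible".

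**The concern.** The protocol's own risk statement describes patients paying less attention to their bodies during training. Its recording method depends on patients noticing a complaint and volunteering it, or on the research team seeing it. A method that waits for reports fits poorly with a hazard of that kind.

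Two things are at stake. The first is completeness: the trial may record fewer events than occur in either group, and an overload problem may be seen late. The second is comparability. The reporters and most of the observers know the allocation, so the share of events captured need not be the same in the two groups, and readers will set the recorded events side by side whether or not a test is planned. The Data monitoring section provides for no monitoring committee and no independent audit, so the event record carries more weight than it otherwise would.

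**Working it through.** The plan gives no figure on this point, so there is none to reproduce. The check is mainly a reading of the sections against one another.

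**1. Is there another route by which events would be elicited?**
- Table 2 (Data collection and outcome measures) lists patient characteristics, questionnaires, movement assessments and adherence. It has no adverse event item at T0, T1, T2 or T3.
- Therapists are asked to monitor progress and to register exercise modifications and attendance. Nothing asks them to record complaints. The article does not say whether they belong to the research team whose observations count.
- Investigators attend only some sessions. Of the 16 supervised sessions (8 weeks × 2), the first 4 are individual and the last 12 are in groups of up to three per therapist.

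**2. Would the questionnaires catch an overload episode?**
- Training runs in weeks 2 to 9. The questionnaires fall in weeks 1, 10, 26 and 52, so none is completed during training.
- The pain ratings cover current pain and the past 7 days (Secondary outcomes). At week 10 that reaches back to about week 9, so a flare that began and settled in weeks 2 to 8 lies outside the window.
- The article states no recall period for the other questionnaires. In any case a score is not an event record.

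**3. What happens to a patient who stops because of a complaint?**
- Statistical analysis omits patients with fewer than 10 sessions and those who drop out before T1.
- Sample size allows drop-outs to be replaced (at most 10), and allocation continues until 30 have completed each intervention.
- Such a patient can therefore be absent from the pain and disability results. The adverse event record is then the main place where the harm could appear.

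**4. What under-capture could do (assumed values, not from the document).**
Let n = 30 per group, p the true risk and s the share captured. The expected number of patients recorded with an event is n × p × s, and the chance that a group records none is (1 − p × s)^30.

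| p | s | Expected recorded | Chance of none |
|---|---|---|---|
| 10% | 100% | 3.0 | 0.042 |
| 10% | 75% | 2.25 | 0.096 |
| 10% | 50% | 1.5 | 0.215 |
| 20% | 100% | 6.0 | 0.001 |
| 20% | 50% | 3.0 | 0.042 |

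With equal capture in both groups the counts fall but their ratio is unbiased. With unequal capture the recorded risk ratio (sensor to static) is the true ratio times s(sensor) / s(static). If the true ratio is 1, capture of 50% against 75% gives 0.50 / 0.75 = 0.67, and the reverse gives 0.75 / 0.50 = 1.5. Both are equally compatible with the text.

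**The case against.** The strongest objection is that only general passive collection is shown, and that a specific bias against the sensor group is not. A reader might infer that the mechanism behind the hazard also suppresses reporting in that group, so that sensor training will look safer than it is. The documents do not support this. Being absorbed in a game does not imply failing to notice or report pain afterwards. Unblinded staff might watch the novel intervention more closely and push the difference the other way. Patients and therapists are also not told the hypotheses. This part of the objection stands in full.

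A reader might also infer that home training makes matters worse for the sensor group, since four of the six weekly exercise occasions are unsupervised. That does not hold either. The sensor system is assigned to the supervised sessions, the home exercises come from a workbook, and both groups have the same number. By planned time, home work is 4 × 5 to 4 × 10 = 20 to 40 min a week against 2 × 20 to 2 × 30 = 40 to 60 min supervised. That is between 20/80 = 25% and 40/80 = 50% of training time.

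It is fair to add that the article plans no formal comparison of harms. Patients are told in writing to report events, and they attend a rehabilitation programme three days a week with many individual sessions. The questionnaires give some cover at T1 and later. These points soften the concern but do not remove it: contact without a set question is still passive collection. The mitigations under Safety considerations bear on how often overload occurs, not on whether it is recorded. Nor is this a detail left to a fuller document, because the article states its collection method.

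**Conclusion.** The concern holds in a limited form. The protocol names an overload risk of sensor training and records adverse events only if they are volunteered or observed. Nothing else shown elicits events between week 1 and week 10, and patients who stop early leave the analysis of the scores that might otherwise show harm. Events may therefore be under-counted in both groups, and with unblinded patients and therapists capture may differ between groups.

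Neither the size nor the direction of any difference can be derived from the document. The figures above rest wholly on assumed risks and capture shares and show only what under-capture could do. The protocol contains no contradiction or misstatement here, and the efficacy analysis is not affected. This is a cheap improvement to a stated method.

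**What to change.** Keep the spontaneous reports. Add one identically worded open question about new or worse complaints, asked in both groups at each supervised session, with the answer recorded alongside attendance, and again at T1. Tabulate events by group for all allocated patients, whatever their attendance and whether or not they drop out.

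Enrolment has already started, and the groups are filled in successive blocks of five by start date. Introduce the question on a single date for both groups and report events before and after that date separately, so that a change in ascertainment is not read as a change in risk or a difference between groups.

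The cost is small: one entry at contacts that already take place, with no extra visit. There are three downsides. More minor events will be recorded in both groups. The answers will be taken by unblinded therapists, so some scope for unequal capture remains. The change may also have to be notified as a protocol modification to the ethics committee, funder, registry and sponsor, as the Dissemination section provides for significant modifications.

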### Data monitoring

The study will be terminated prematurely if decided so by: the board of physiatrists from the MRC or the board of the MRC. There is no data monitoring committee or independent audit for this study.

## Discussion

In this study, the effect of a sensor-based spinal movement control intervention on the movement control of the spine in low back pain patients over the course of a multidisciplinary rehabilitation programme will be compared to the effect of conventional static motor control exercises. In addition, we aim to evaluate the effect of the intervention on disability, pain intensity, fear avoidance beliefs and health related quality of life. Finally, therapy adherence will be compared between the interventions. Sensor-based exergames are a relatively new tool to train spinal movement control using meaningful and engaging feedback. To our acknowledge, this is the first study which evaluates if sensor-based exergames training influences movement control of the spine in low back pain patients to a greater extent than static motor control training.

Currently, there is no gold standard to assess movement control of the spine. Therefore, we will analyse our main outcome with three different assessments: [1] sensor-based tracking tasks on a laptop, based on a tracking task from Willigenburg et al. (12), [2] the clinical movement control test battery of Luomajoki et al. (19, 20) and [3] a self-developed clinical movement test battery. Because these tests are performed in the same subjects at the same moment, the results of this study could provide us more insight in how to assess movement control of the spine. The reliability and minimal detectable changes of the movement control tracking tasks and the self-developed clinical movement test battery are not available which may bias the outcome of the study.

There are several limitations of this study that need to be addressed. Our study population completely consists of Dutch military personnel. The Dutch military population mostly consist of males, who are relatively young and physically active compared to the civilian population (34). The cause of low back pain in this population is mostly overuse, due to the high workload in the Netherlands Armed Forces (34, 35). For this reason, the generalizability of the results of this study might be compromised. Another limitation, from a clinical perspective, is that the main outcome of this study (spinal movement control) does not correspond to the main focus of most patients, which is reducing pain and/or disability. Although these outcomes will be assessed, the study might be underpowered to demonstrate significant effects on these domains for at least two reasons. First, some patient subgroups may derive a greater benefit from one type of exercise than another (e.g., static motor control vs. sensor based movement control) because of the heterogeneity in the low back pain population. Exploratory analyses can be performed to evaluate if these subgroups appear to exist, but a larger sample is expected to be required to provide more conclusive evidence. Second, because this study is embedded in a multidisciplinary rehabilitation program, an effect of the tested intervention on pain or disability might be hidden by the effect of other components of the program. Finally, for the main outcome of this study, movement control of the spine, the effect of other therapies might reduce the contrast between groups as well. It cannot be excluded that patients in the static motor control group will also receive exercises of the movement control group during other therapies and vice versa. This can be considered a study confounder. However, we hypothesize that it is relatively difficult to improve spinal movement control without the use of sensors. Embedding this study within a multidisciplinary rehabilitation program could be considered a test of this assumption. Each week of the intervention consists of two supervised therapy sessions of 20–30 min and four non-supervised home exercises of 5–10 min. Although therapists will encourage patients to do their home exercises, compliance can influence results in this study. For this reason, self-reported exercise adherence will be measured in both groups.

The results of this study will help to inform clinicians and researchers on the efficacy of movement control training in combination with multidisciplinary rehabilitation programme for patients with low back pain. Also it will enlighten preliminary impacts of the interventions on patient reported outcomes. This could directly affect decision making in clinical practice and culminate in larger trials to assess if pain and/or disability could be reduced by movement control training in (subgroups of) low back pain patients.

## Ethics and dissemination

### Ethical considerations

This study will be performed in accordance with the Declaration of Helsinki. Ethical approval was obtained from the Medisch Ethische Toetsingscommissie (METC) Brabant on 14 Mai 2021 and all procedures will be conducted in accordance with the statement conducting research involving humans. Informed consent will be obtained by the investigators from all potential patients and patients will be aware that participation is voluntary and can withdraw from the study at any time.

### Safety considerations

The tests at the beginning and end of the intervention could result in a transient increase in low back pain. Training with sensors could result in spinal tissue overload as a result of lack of focus on bodily sensations. However, the Military Rehabilitation Center has more than 10 years of experience with providing a similar type of therapy in low back pain patients. Moreover, the complexity, duration and intensity of the exercises will be increased gradually, which would minimize the chance of overloading the spinal structures. Damage to research subjects through injury or death caused by the study is covered by the Ministry of Defense. This applies to the damage that becomes apparent during the study or within 4 years after the end of the study.

### Dissemination

To protect confidentiality, personal information about the patients will be collected, shared and maintained in a database on a secured computer that can only be accessed by principal investigators before, during and after the trial.

Any significant modifications of the study protocol will be communicated to the METC, trial funder (SZVK), Open Science Framework Registries and the trial sponsor (MRC). The investigators will communicate trial results to the patients, trail sponsor, METC and funder within 1 year after the end of the study. The study results shall be presented at symposia, conferences and to publish in journals and theses without publication obligations from the sponsor.

## Ethics statement

The studies involving human participants were reviewed and approved by Medisch Ethische ToetsingsCommissie (METC) Brabant. The patients/participants provided their written informed consent to participate in this study. Written informed consent was obtained from the individual(s) for the publication of any potentially identifiable images or data included in this article.

